#### Waiting list control group

Participants whose group was cluster-randomized to the WL condition are not offered group sessions until 16 weeks have passed. During this period, adolescents may seek any kind of treatment as usual, including medication for co-occurring disorders or any kind of SUD treatment. Afterwards, DELTA-JU is provided in the same way as in the immediate treatment condition described above. The pre-treatment waiting period acts as a naturalistic comparator to the treatment. It is a suitable comparator given that many of the possible confounders (housing, timespan since previous detoxification treatment, availability of concurrent treatments/medication, psychosocial support, schooling situation etc.) should be equally present or absent in both conditions. Since concomitant treatments are allowed and documented in both conditions, we will be able to control for this confounder while at the same time providing a comparator group that represents the heterogeneity of SUD care in this population.

#### One-day workshop for personnel

The workshop will be based on content both from the parental education group (see Table 2) and previous presentations held for personnel of county administrations, medical students, police officers, teachers, and educators. If applicable, we may use computerized presentations, videos, worksheets, role play instructions, case vignettes, panel discussions etc. as educational methods.

### Quantitative measurements

Primary outcomes in terms of study aims for adolescents are SUD-related subjective utility (GEJ), substance-related craving as a measure of relapse risk (MaCS), SUD severity (AUDIT, DUDIT, and FTND), and self-reported past-month tobacco use (substance use interview). For personnel, primary outcomes are SUD-related subjective utility and satisfaction ratings concerning the workshop organization (GEB-K, GEB-S). Secondary outcomes for adolescent participants are similar to those from the DELTA evaluation study (15) and include psychopathologies (BDI-II, PQ-16, UCLA-PTSD, and YSR), life satisfaction (SWLS), and perceived stress (ERI-S-10, PSS-10). For sample characterization, check of inclusion criteria, and for exploratory analysis in combination with data from that study, we will also apply additional measures that are either clinical standard in our outpatient clinic (e.g., tests of intelligence or cognitive performances) or that are of research interest yet not related to the main study aims (e.g., analysis of epigenetics in blood, cortisol in saliva and hair). Table 3 lists all quantitative measures which are applied in the DELTA-JU study to obtain outcomes. Measures related to study hypotheses (AUDIT, DUDIT, FTND, MaCS, GEJ, GEB, and substance use interview), exploratory hypotheses (BDI-II, ERI-S-10, PQ-16, PSS-10, SWLS, UCLA-PTSD, and YSR), study inclusion (MINI-KID, C-DIPS) as well as measures which were generated (GEJ, GEB) or adapted (MQ-RS, CO in breath, physical examination) for this study are presented in more detail with references to their German versions. It should be noted that items from several instruments had to be reworded so that the formal German addressing of participants (“Sie,” “Ihr”) is replaced with the informal German addressing (“Du,” “Dein”) that is more adequate when addressing children and adolescents. Details for other instruments and procedures can be found in the referenced sources.

**Table 3 tab3:** Assessment instruments for adolescent participants as well as personnel of youth welfare institutions (highlighted with *).

Construct	Reference	Instrument used per assessment		
		PRE (week −16)	Baseline (week 0)	FU (week 16)
Domain: Evaluation of intervention				
Increase in subjective utility, skills	(15)	–	–	GEJ
Increase in subjective utility, skills	–			GEB-K*
Satisfaction with one-day workshop	–	–	–	GEB-S *
Satisfaction with DELTA-JU group session (after each session)	(34)	–	GTS-P	–
Satisfaction with DELTA-JU group session (after each session)	(34)	–	GTS-T^a^	–
Domain: Substance use and SUD				
Substance use (generic interview)	(5)	interview	interview	interview
Diagnosis of SUD, co-occurring mental disorders	(35, 61, 62)	C-DIPS/ MINI-KID	C-DIPS/ MINI-KID	C-DIPS/ MINI-KID
Severity of SUD: Alcohol use disorder	(36)	AUDIT	AUDIT	AUDIT
Severity of SUD: SUDs for illicit substances	(37)	DUDIT	DUDIT	DUDIT
Severity of SUD: Tobacco use disorder	(22)	FTND	FTND	FTND
Craving for substance use	(38)	MaCS	MaCS	MaCS
Domain: Co-occurring psychiatric problems				
Depressiveness	(39)	BDI-II	BDI-II	BDI-II
Psychotic symptoms	(40)	PQ-16	PQ-16	PQ-16
Psychopathologies	(58)	YSR	YSR	YSR
Satisfaction with life	(41)	SWLS	SWLS	SWLS
Traumatic events and post-traumatic problems	(42)	UCLA PTSD	UCLA PTSD	UCLA PTSD
Perceived stress	(43)	PSS-10	PSS-10	PSS-10
Perceived stress	(44)	–	ERI-S 10*	ERI-S 10*
Domain: Risk factors for substance use and SUDs				
Tobacco use: motives	(45) ^c^	MQ-RS	MQ-RS	MQ-RS
Tobacco use: expectancies	(46) ^c^	SEQ	SEQ	SEQ
Tobacco abstinence: self-efficacy	(47)	SER	SER	SER
Tobacco abstinence: percentage of smoking peers	(48)	PSP	PSP	PSP
Temperament	(49)	SURPS	SURPS	SURPS
Sociodemographics (generic questionnaire)	(5)	–	Generic ^b^	–
	–	–	Generic*	–
Domain: Cognitive functioning				
Memory	(50)	VLMT	VLMT	VLMT
Alertness, divided attention, inhibition/impulsivity	(51)	TAP	TAP	TAP
General executive functioning	(52)	Stroop	Stroop	Stroop
	(52)	Stop-signal	Stop-signal	Stop-signal
Intelligence	(53, 54)	–	WISC-V / WAIS-IV ^d^	–
Domain: Biological markers of substance use and stress				
Carbon monoxide in exhaled breath	(22)	CO in air	CO in air	CO in air
Genome wide DNA methylation	(55)	Blood	Blood	Blood
Cortisol Cortisol	(56) (56)	Saliva Hair	Saliva Hair	Saliva Hair
Weight, height, acute physical diseases	–	examination	examination	examination
Pubertal development (questionnaire)	(57)	PDS	PDS	PDS

* self-report of personnel. ^a^ group of adolescents is rated by the therapist. ^b^ individual adolescent is rated by legal guardian. ^c^ translated or adapted for this study. ^d^ WISC until age 16, WAIS for older adolescents.

#### Severity of SUDs

Severity of SUDs is measured via three total scores of self-report instruments assessing substance use parameters as well as related problems. The Fagerström Test for Nicotine Dependence (FTND) (22) has six items with 2–4 answer options per item, resulting in a total score of 0–10 points with higher points indicating stronger problems due to tobacco use in the past week. The Alcohol Use Disorders Identification Test (AUDIT) (36) has 10 items with 3–5 answer options resulting in a total score of 0–40 points for alcohol-related problems in the past 12 months. The Drug Use Disorders Identification Test (DUDIT) (37) has 11 items with 3–5 answer options, resulting in a total score of 0–44 points for drug problems in the past 12 months.

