#### Setting specifics in content

In our outpatient facility, adolescents may or may not yet have reached abstinence at the beginning of treatment (15). Thus, DELTA aimed at reducing substance use, achieving point abstinence, and finally achieving continuous abstinence (12). The initial sessions therefore focus on motivational techniques to reinforce commitment to achieve abstinence. In contrast, those in youth welfare institutions generally are abstinent with the start of their stay (15). In most cases they underwent inpatient detoxification before being transferred to the youth welfare institution. Thus these adolescents may already have gained SUD-related knowledge (“subjective utility”) and may already be motivated to remain abstinent rather than becoming abstinent. Not surprisingly, the evaluation study showed lowest satisfaction of adolescents with content regarding “strategies to reduce fear, to increase SUD-related subjective utility, and to reignite self-confidence in patients” (15). Therefore, it seems adequate to reframe respective sessions to fit setting-specific needs. Adolescents in these institutions live there full-time following structured routine involving psychological care, schooling, household chores, exercise, and other activities. They are under supervision continuously and are only allowed on weekends depending on their participation and commitment to institutional rules. Medical care (including psychiatric medication) is not provided by internal staff but is accessed the same ways as for other adolescents (appoints at external institutions/psychiatrists).

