#### Sampling stage

During the sampling stage in months 5–22, adolescents will be recruited in cooperating youth welfare institutions in the study region, followed by a group-wise cluster-randomization. Adolescent participants will be prospectively assessed both at baseline (BL, a week before the intervention starts) and at follow-up (FU, 16 weeks after first group session). Those in the WL group will receive an additional pre-assessment (PRE, 16 weeks before intervention starts) for the WL to control for natural development. Assessments will take place in the youth welfare institution if possible, or in our outpatient clinic, e.g., for physical examinations. Questionnaires will be filled out in participant’s free time. Participants will be reimbursed at PRE (15 EUR), BL (20 EUR), and FU (40 EUR). The DELTA-JU group and individual sessions will be carried out as outlined below (“Interventions”) with possible changes due to the revision process. Study team members (i.e., psychologists, medical doctors, doctoral students, and student assistants from psychology, medicine, social work, or similar) who conduct the sessions or any assessment will be trained and supervised by the principal investigators.

During the same time, personnel from the youth welfare institutions will receive the revised one-day workshop on SUD-relevant topics. Workshops will be carried out either in the institutions themselves, in our outpatient clinic, in a public place, or via video conference if necessary due to restrictions for the prevention of COVID-19 infections. Whenever possible, personnel from similar institutions will be allowed to participate in the workshop. Personnel will also be assessed twice (BL at beginning and end of the workshop day, FU 16 weeks later) with questionnaires regarding the evaluation of workshop content and organization. All procedures were conducted in accordance with the Declaration of Helsinki, publicly pre-registered and approved by the local Institutional Review Board (see “Ethics” section below). For details on the dissemination stage, see "Dissemination” section below. The treatment and measurement schedule is shown in Figure 3.

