#### Substance use

Substance use is assessed via structured interview (5) by a clinical psychologist who asks for the number of use days and the amount per use day on average for each of the following substances both for past month and past year: nicotine, alcohol, cannabis, methylenedioxymethamphetamine (MDMA), amphetamine, methamphetamine, hallucinogens, opiates, inhalants, or other. These quantity and frequency reports are multiplied to obtain a quantity-frequency index (e.g., for alcohol: 10 drinking days past month × 4 standard drinks per drinking occasion = 40 consumption units per month during the past year). Additionally at BL, the interviewer will ask the same questions for past year-use as well as for age at first use per substance. Changes in the past-month quantity-frequency index for tobacco use will be a primary outcome. Other substances are only explored given that youth welfare institutions do not permit any other substance use than smoking.

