#### Hypotheses

Aim (A) is reached when for each need, identified through qualitative analyses of interviews, one or more adjustments to the content or procedure of DELTA-JU is documented. No quantitative hypothesis is applicable. Aims (B) and (C) are achieved through testing the following hypotheses in adolescents who are abstinent for alcohol and drugs except nicotine/tobacco:
Adolescents: relevant increase in SUD-related subjective utility through FU (descriptive: a medium rating of 2.0 or higher in the respective GEJ items across participants);Adolescents: significant reduction of substance-related craving as a measure of relapse risk (*p* < 0.05, MaCS score) through FU;Adolescents: significant reduction of SUD severity (*p* < 0.05, scores of FTND, AUDIT, and DUDIT) through FU;Adolescents: significant reduction of self-reported past-month tobacco use through FU (*p* < 0.05, substance use interview);Personnel: relevant increase in SUD-related subjective utility through FU (descriptive: a medium rating of 2.0 or higher in the respective GEB items across participating personnel); andPersonnel: high satisfaction ratings concerning the workshop organization (descriptive: a medium rating of 4.0 or higher in the respective GEB items across participating personnel).

Additionally, secondary outcomes in adolescents (BDI-II, PQ-16, UCLA-PTSD, PSS-10, and SWLS) and personnel (ERI-S-10) will be tested exploratorily for changes through FU as previously done in the DELTA evaluation (15). All reductions through FU in adolescents are expected to be descriptively larger than reductions over the natural course, i.e., from PRE to BL in the WL group.

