### Strengths and limitations

The presented study design has several strengths. First, it is in line with ethical requirements that all adolescents are offered treatment. Waiting for 16 weeks in the WL condition still seems adequate given that adolescents may reside for up to 2 years in youth welfare institutions. In randomized clinical trials, for example, only cases may have received treatments. Second, it requires a smaller sample when participants become part of several analysis groups (intervention vs. WL). Third, alternative explanations of time effects may be controlled for by comparing BL-FU effects with PRE-BL effects.

Challenges arise from uncontrolled parallel treatments during the waiting period. Such treatments cannot be included in the quantitative estimation of treatment effects due to the limited number of participants in each group. Furthermore, homogeneity of cooperating youth welfare institutions is limited. Results may thus have to be replicated in other and diverging institutions. Although the sample size was *a-priori* calculated to maximize the use of available resources, drop-out rates may be unexpectedly high. In this case, additional participants and institutions may have to be recruited. In case of limited sample size, using Bayesan methods instead of testing for differences from zero may be advisable (74). Both the AUDIT and DUDIT have been previously used to assess changes in alcohol- and drug-related problems in adolescents and young adults using 3-month intervals between BL and FU (75, 76). Nevertheless, it remains possible that small changes in problems might go unnoticed given that both instruments cover 12 month periods. Another limitation arising from the limited sample size in a phase II study is the impossibility to adjust for several baseline variables. Such superior analysis strategies are not feasible at this point of the intervention development but will be imperative during phases III/RCT and phase IV studies in the future. The same holds true for the analysis of relevant patient subgroups (e.g., differentiating those with primarily alcohol-related problems from those with primarily cannabis-related problems) and intention-to-treat analyses or sensitivity analysis. Finally, additional measures that would objectify relapse to the use of alcohol or other drugs were not funded and will have to be implemented in a future trial, preferably a multi-center RCT testing DELTA-JU against treatment-as-usual.

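### AUDIT and DUDIT recall 12 months but are compared over about 17 weeks in mostly abstinent residents, so both scores tend to drift down without any intervention effect

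*Protocol article*

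**What the plan says.** All references are to the protocol article.

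- **Recall period.** Under Severity of SUDs, the AUDIT is described as "resulting in a total score of 0–40 points for alcohol-related problems in the past 12 months" and the DUDIT as "resulting in a total score of 0–44 points for drug problems in the past 12 months". FTND refers to the past week.
- **Timing.** Under Sampling stage, adolescents are "prospectively assessed both at baseline (BL, a week before the intervention starts) and at follow-up (FU, 16 weeks after first group session"). That puts about 17 weeks between the two assessments.
- **Population.** Under Setting specifics in content, "those in youth welfare institutions generally are abstinent with the start of their stay", and "In most cases they underwent inpatient detoxification before being transferred to the youth welfare institution". The Hypotheses section speaks of "testing the following hypotheses in adolescents who are abstinent for alcohol and drugs except nicotine/tobacco".
- **Role.** Quantitative measurements lists AUDIT and DUDIT among the primary outcomes. Hypothesis 3 expects significant falls in FTND, AUDIT and DUDIT at p < 0.05.
- **Test.** Under Data analysis, a repeated measures MANOVA with time as the factor is run on all 40 analysed adolescents. A significant BL-FU reduction across the five metric outcomes is taken to show a relevant intervention effect, and between-group effects are described as unimportant.
- **Waitlist period.** Under Hypotheses, BL-FU reductions are expected to exceed the waitlist's PRE-BL reductions descriptively. Strengths and limitations adds that this comparison may control for other explanations of change over time.
- **Stated limitation.** Strengths and limitations says that "it remains possible that small changes in problems might go unnoticed given that both instruments cover 12 month periods".

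**The concern.** A 12-month score taken 17 weeks after another 12-month score mostly describes the same year. The two scores differ only in the oldest 17 weeks, which drop out, and the newest 17 weeks, which come in. In this setting the oldest weeks are likely to be weeks of use before admission, and the newest are expected to be weeks of supervised abstinence. Moving the window therefore pushes both scores down, whatever the intervention does.

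The primary test has no comparator that would remove this movement. It attributes the BL-FU change to the intervention, so the drift counts towards success in two of the five scores and in hypothesis 3. The article discusses the 12-month window, but only as a reason why real change might be missed. The risk of an apparent change with no real effect is not stated.

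**Working it through.** **1. The plan's own sample size.** Inputs from Estimation of sample size: f = 0.40, r = 0.1, α = 0.05, power 0.95. For a within-person time effect with two measurements, λ = f² × N × 2 / (1 − r).
- N = 39: λ = 0.16 × 39 × 2 / 0.9 = 13.87, power 0.952.
- N = 40: λ = 14.22, power 0.957.

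The stated 40 therefore reproduces, as does 40 / (1 − 0.20) = 50 enrolled. The sample size is not in dispute. The standardised paired change that it implies is dz = 2 × 0.40 / √(2 × 0.9) = 0.60.

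**2. Overlap of the two windows.** With a 52-week recall and a gap of 17 weeks (16 by the column labels of Table 3), the windows share 52 − 17 = 35 weeks (67%), or 52 − 16 = 36 weeks (69%).

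**3. Weeks of use inside the window, with no intervention effect.** Assumptions, none of them given in the article: steady use until the last use, A weeks before BL, and complete abstinence afterwards. Use-weeks at BL = 52 − A. Use-weeks at FU = max(0, 52 − A − gap).

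| Last use before BL (A) | BL | FU, gap 16 / 17 | Fall |
|---|---|---|---|
| 0 weeks | 52 | 36 / 35 | 31% / 33% |
| 4 weeks | 48 | 32 / 31 | 33% / 35% |
| 12 weeks | 40 | 24 / 23 | 40% / 43% |
| 26 weeks | 26 | 10 / 9 | 62% / 65% |
| 36 weeks | 16 | 0 / 0 | 100% |
| 52 weeks or more | 0 | 0 | no drift |

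These are shares of use-weeks, not AUDIT or DUDIT points.

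**4. What a drift would do to the test.** The standardised size of the drift is unknown, so a range is assumed. The table gives the probability of p < 0.05 at N = 40 with a true intervention effect of zero. The first column is a two-sided paired t-test on one score. The second is a paired Hotelling test on five outcomes in which only AUDIT and DUDIT drift; its range covers a correlation between those two changes from 0.5 down to 0, with the other outcomes uncorrelated.

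| Assumed drift dz | One score | Five-outcome test |
|---|---|---|
| 0 | 5% | 5% |
| 0.2 | 23% | 15-21% |
| 0.3 | 46% | 30-45% |
| 0.4 | 69% | 52-72% |
| 0.5 | 87% | 74-91% |
| 0.6 | 96% | 90-98% |

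A drift as large as the effect that the trial is powered for (dz = 0.60) would nearly always be significant. Much smaller drifts already take the error rate well above 5%.

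**The case against.** **Use-weeks are not score points.** Both totals are built from items with 3-5 answer options and also cover related problems. A resident with several months of use still in the window might give the same answers twice. This stands: the percentages show the direction and the mechanism, not the size of the fall in either score.

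**The drift does not affect everyone.** The article says that residents are generally abstinent and in most cases detoxified, not that all are. Chronic past use is enough for inclusion, and stays can last up to two years. A resident whose last use was over 12 months before BL has nothing left to leave the window, and relapse works against a fall. This stands too. A reader might infer that a fall is guaranteed; the documents support only a tendency, in those who used within the year before BL and stay abstinent.

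**The waitlist's PRE-BL change is a safeguard.** AUDIT and DUDIT are also taken at PRE, and that interval shows the same kind of drift, so the comparison could expose it. But it is descriptive, lies outside the test and decides nothing. Within the waitlist arm it is also imperfect, because PRE-BL lies closer to admission than BL-FU.

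**Two scores cannot win the trial.** A reader might infer that AUDIT and DUDIT alone could establish overall success. If a fall in every metric outcome is required, they cannot, because FTND (past week) and past-month tobacco use are unaffected. Their part of hypothesis 3 is still biased towards success. If a significant multivariate test is enough, the drift also feeds that test.

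**Different treatment of the interview data.** The article says of the interview measure that "Other substances are only explored given that youth welfare institutions do not permit any other substance use than smoking". A reader might see a contradiction in keeping AUDIT and DUDIT primary. A 12-month problem score is a different measure from a past-month use index, so this is not one.

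**Precedent.** The article cites earlier use of both instruments over 3-month intervals. Those sources are not at hand, and the precedent as described does not address drift in a sample that is already abstinent.

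**Conclusion.** The point holds as a bias of known direction and unknown size. It rests on four facts in the article: a 12-month recall, about 17 weeks between assessments, a population generally abstinent from admission, and a pooled before-after change read as an intervention effect. For residents who used in the 12 months before BL and remain abstinent, AUDIT and DUDIT tend to fall without any effect of DELTA-JU.

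The size in score points cannot be derived, because time since last use, score means and SDs are not given. The loss of about one third of use-weeks when last use was at BL, rising for earlier last use and absent beyond 12 months, is an illustration that rests on steady earlier use and full abstinence. The error rates in the working depend in addition on an assumed standardised drift. Two of the five metric outcomes are affected. The stated limitation covers only the opposite risk.

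**What to change.** Do not read a BL-FU fall in AUDIT or DUDIT as an intervention effect. Choose one of the following:

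1. Treat both scores as exploratory in the before-after test.
2. Judge them only by the immediate arm's BL-FU change against the waitlist's PRE-BL change over the same weeks. The drift cancels only as far as the arms are similar in time since last use, which alternating assignment of a few institutions does not assure, so report that time by arm. Also check the interval lengths: Table 1 puts both at week 0 to week 17, but the Sampling stage text implies 16 − 1 = 15 weeks for PRE-BL against 17 for BL-FU.

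In either case, add to Strengths and limitations that the 12-month window can lower both scores on its own.

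The change is to analysis wording and uses data already planned at PRE, BL and FU. The cost is that hypothesis 3 then rests mainly on FTND, or on a contrast with less power than the pooled test.

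Shortening the recall period is not advised. Enrolment has begun, and the item rewording described under Quantitative measurements concerns only the form of address, so it gives no basis for changing the instrument mid-trial.
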